### Outcomes

We will study the following feasibility outcomes:

The number of eligible patients who are approached.The proportion of those approached who consent to participate in the study.The completeness of data collection.The completeness of follow-up.The number and proportion of patients with neurosurgically significant TBI.Determination of the interobserver reliability of the CCHR completed by prehospital care providers and ED physicians.Determination of the interobserver reliability for each component of the CCHR assessed by prehospital care providers and ED physicians.The diagnostic performance and clinical sensibility of the CCHR in the opinion of attending paramedics.Determination of the acceptability of trial processes as perceived by paramedics and patients.

### Measuring and defining outcomes

Feasibility outcomes will be assessed using screening logs and case report forms (CRFs) completed by attending paramedics during the course of the study. At the end of the study period, a minimum of two clinicians (affiliated with the relevant NHS trusts) will review in-hospital patient records to diagnose the secondary outcomes of this feasibility study (neurosurgically significant TBI, abnormal CT findings and death within 7 days). A third independent investigator will be invited to adjudicate any discrepancies. Diagnostic adjudication will be blinded to the final interpretation of the CCHR. Additionally, a neuroradiology consultant/expert will be consulted in case of the CT scan diagnosis is inconclusive.

Neurosurgical interventions are defined as any neurosurgical intervention including intracranial pressure monitoring or an Abbreviated Injury Scale (AIS) with the severity ≥3 in the head region. Abnormal head CT findings will be classified as normal or abnormal and are defined as at least one of the following: skull fractures, intracranial lesions, such as cerebral contusion and traumatic intracranial haemorrhages, or other clinically significant findings requiring hospital admission, neurosurgical interventions and routine follow-up.

### Data collection

#### Prehospital setting

During the study period, all patients will receive standard prehospital care in accordance with local guidelines. Prior to their participation in the study, all participating paramedics will be provided with bespoke training specifically designed for the study. This training will cover all aspects of the study protocol, including eligibility assessment, the consent process, data collection procedures and guidance on interpreting the CCHR. To ensure accessibility and flexibility, the training will be offered both face-to-face and through various online sessions conducted via Zoom. Additionally, the training sessions have been recorded and made available online for those unable to attend live. This approach allows paramedics to access the training material at their convenience, ensuring that all participants receive comprehensive training in the study protocols and data collection methods.

Prehospital data will be collected using Research Electronic Data Capture (REDCap), a secure web-based platform hosted at the University of Manchester. REDCap is a software application that was created to facilitate the process of collecting and managing research data. Prior to recruitment, a training session will be held to equip participating sites with data collection skills. In addition, paper CRFs will be available as an alternative method of data collection. It is expected that this approach will provide flexibility and ensure continuity in data collection. A variety of data will be collected in the prehospital setting, including, but not limited to:

Baseline demographics information (ie, gender–age).Anticoagulant use.Injury characteristics (ie, mechanism of injury, place).Medical history.Initial chief complaint (ie, vomiting, headache, loss of consciousness, amnesia).Prehospital physiological parameters (ie, GCS, vital signs).Clinical criteria required to use the CCHR.Destination hospital.

Paramedics will record these data contemporaneously, either prior to or immediately following handover at hospital.

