**Methods and analysis:**

We will recruit adult patients who are being transported to an emergency department (ED) by ambulance after suffering a mild TBI. Paramedics will prospectively collect data for the CCHR. All patients will be transported to the ED, where deferred consent will be taken and the treating clinician will reassess the CCHR, blinded to paramedic interpretation. The primary clinical outcome will be neurosurgically significant TBI. Feasibility outcomes include recruitment and attrition rates. We will assess acceptability of the CCHR to paramedics using the Ottawa Acceptability of Decision Rules Instrument. Interobserver reliability of the CCHR will be assessed between paramedics and the treating clinician in the ED. Participating paramedics and patients will be invited to participate in semistructured interviews to explore the acceptability of trial processes and facilitators and barriers to the use of the CCHR in practice. Data will be analysed thematically. We anticipate recruiting approximately 100 patients over 6 months.

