### Objectives

To determine the feasibility of a study to evaluate the diagnostic accuracy of the CCHR in the prehospital environment.To evaluate the interobserver reliability of the CCHR between prehospital clinicians and ED physicians.To evaluate the clinical sensibility of using the CCHR in the prehospital environment and to measure paramedics’ attitudes toward the CCHR.To obtain an estimate of the diagnostic accuracy of the CCHR when used in the prehospital setting.

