#### In-hospital environment

REDCap will be used to collect hospital data, and a paper CRF will also be available as an alternative. Emergency physicians at the receiving hospital will assess the patients to determine whether a CT scan is necessary in accordance with local and national guidelines. Relevant data about imaging studies undertaken and their findings will be extracted from hospital records. The routine radiology reports will be used to extract the follow-up data required for this study. Where there is uncertainty about the interpretation of the radiology report, a second radiologist will be asked to interpret the images.

Further, emergency physicians at the receiving hospitals will be asked to assess the patients using the CCHR and record their findings, blinded to the assessments made by participating paramedics. These data will be used to determine the interobserver reliability of the CCHR between paramedics in the prehospital environment and clinicians in the ED. Additionally, in-hospital medical records will be reviewed to obtain information regarding neurosurgical interventions undertaken during the patient’s hospital admission.

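### Paramedics may record the CCHR after hospital handover with no stated blinding to ED information, so paramedic–ED agreement may be inflated by an unknown amount

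*Protocol article*

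**What the plan says.** The Prehospital setting section of Data collection lists what paramedics collect. One entry is "Clinical criteria required to use the CCHR". The timing rule for the whole list follows: "Paramedics will record these data contemporaneously, either prior to or immediately following handover at hospital". The abstract adds "Paramedics will prospectively collect data for the CCHR".

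Blinding is stated in two places:
- **ED rating.** In the In-hospital environment section, emergency physicians are "asked to assess the patients using the CCHR and record their findings, blinded to the assessments made by participating paramedics". The abstract agrees: "the treating clinician will reassess the CCHR, blinded to paramedic interpretation".
- **Outcome review.** Measuring and defining outcomes says "Diagnostic adjudication will be blinded to the final interpretation of the CCHR".

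The article does not say that paramedics are kept from hospital information before they complete the form, that the form is closed at handover, or that its completion time is recorded.

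One objective is "To evaluate the interobserver reliability of the CCHR between prehospital clinicians and ED physicians". The Outcomes section lists agreement both for the rule as a whole and for each component. The Quantitative data section analyses agreement with Cohen's kappa and 95% CIs, and gives sensitivity, specificity and likelihood ratios against a reference standard taken from hospital records.

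**The concern.** Kappa describes agreement between two ratings made separately. Here one direction of influence is closed, since the ED physician does not see the paramedic's rating. The other is left open. Handover is a conversation with hospital staff, and items such as GCS, vomiting, amnesia or medication may be clarified in it. A form completed afterwards can take up those clarifications. If that moves paramedic ratings toward the ED answer, kappa rises for a reason unrelated to how reliably the rule works in the field. The paramedic rating is also the index test for the accuracy estimates, so they are exposed to the same late information.

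A second issue does not depend on any contamination. The Introduction proposes the rule as a help in choosing the destination or leaving a patient at scene. A form written after arrival does not show that the rule was worked through when such a decision would be taken, and showing this is part of what a feasibility study of prehospital use should do.

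**Working it through.** **1. Passages side by side.**

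| Rating or review | Protected from | Where stated |
|---|---|---|
| ED physician's CCHR | Paramedic's assessment | Abstract; In-hospital environment |
| Outcome adjudication | CCHR interpretation | Measuring and defining outcomes |
| Paramedic's CCHR | Nothing stated; recording allowed after handover | Prehospital setting |

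The exposure follows from a timing rule that the article states, not only from omitted detail.

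**2. What could happen to kappa.** No figure in the article depends on this point, so there is none to reproduce. The following is illustration only.

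Assumed inputs:
- k, the kappa that would be seen with separate ratings;
- p, the proportion positive, equal for both raters;
- f, the share of forms completed after handover;
- c, the share of disagreements in those forms that are changed to the ED answer, equally in both directions, so that p stays the same for both raters.

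The article gives none of these.

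Chance agreement is pe = p² + (1 − p)², so 1 − pe = 2p(1 − p). True disagreement is d = 2p(1 − p)(1 − k). With q = f × c, observed disagreement is d(1 − q). Then

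observed kappa = 1 − d(1 − q)/(1 − pe) = 1 − (1 − k)(1 − q) = k + q(1 − k),

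which does not depend on p.

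For k = 0.60:

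| f | c | q | Observed kappa |
|---|---|---|---|
| 0 (or any f with c = 0) | – | 0 | 0.60 |
| 25% | 10% | 0.025 | 0.60 + 0.025 × 0.40 = 0.61 |
| 50% | 10% | 0.05 | 0.62 |
| 50% | 25% | 0.125 | 0.65 |
| 50% | 50% | 0.25 | 0.70 |
| 100% | 50% | 0.50 | 0.80 |

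Over the five non-zero cases, a true kappa of 0.40 reads 0.415 to 0.70, and a true kappa of 0.80 reads 0.805 to 0.90.

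**3. Against sampling error.** The article expects about 100 participants. The simple large-sample standard error is √[po(1 − po)/(n(1 − pe)²)], where po is observed agreement. At k = 0.60 and p = 0.5, po = 0.80 and pe = 0.50, so SE = √(0.16/25) = 0.08 and the 95% half-width is 1.96 × 0.08 = 0.157. At p = 0.7 it is 0.174, and at p = 0.9 it is 0.281. The shifts of 0.01 to 0.10 in the first four non-zero rows are smaller than any of these. Only the last row's shift, 0.20, exceeds the half-width, and then only at p = 0.5 or 0.7. A systematic shift is, however, not reflected in the confidence interval, whatever its size.

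**4. Cost of dropping late forms.** If half the forms were late, about 50 would remain and the half-width would grow by √2: 0.157 × 1.414 = 0.22 at p = 0.5, and 0.174 × 1.414 = 0.25 at p = 0.7. If all were late, none would remain.

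**The case against.** A reader might infer that the paramedic rating is not independent of the ED rating and that kappa is biased upward. The article does not support that, for these reasons.

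- **Writing late is not judging late.** The timing sentence asks for contemporaneous recording and ends the window straight after handover. The abstract calls the collection prospective. A paramedic may write down afterwards a judgement already made at scene.
- **The route is not shown.** Nothing says that the ED physician's CCHR, a CT decision or a CT result exists, or reaches the paramedic, at that moment. Age and mechanism leave little room for influence.
- **The direction is not certain.** Recall error in a late form, or real clinical change between scene and ED, would lower agreement.
- **The stakes are limited.** The article calls the analyses exploratory and descriptive, and no progression criterion in Table 2 uses kappa, accuracy or form timing. Outcome review is blinded to the CCHR interpretation, so the accuracy concern is weaker than the agreement concern.
- **Practicality.** A flexible window suits emergency work, and an article may leave form fields and training instructions to the full protocol.

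All of this limits the size of the problem, and the first three points rule out calling the bias established. The exposure itself remains. The requirement for contemporaneous recording does not remove it, because the same sentence counts a form completed after handover as meeting it. Missing form detail alone would be no finding, but the permission to record late is in the text.

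**Conclusion.** The point holds as a risk. The article lets the CCHR criteria be recorded after handover and states no blinding of paramedics to ED information, although the other two assessments are blinded. Agreement, and possibly accuracy, may be inflated. Neither the existence nor the amount of inflation can be derived from the article: the 0.60 to 0.80 range for a true kappa of 0.60 rests wholly on assumed shares of late forms and altered ratings, and the milder cases lie well inside sampling error at 100 patients. Separately, a late form is weak evidence that the rule was applied at the time a transport decision would be made.

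This is a cheap improvement and not a threat to the study's conclusions. It is still worth making, because the results are meant to inform the design of the definitive accuracy study and, without completion times, the effect could not be shown to be small.

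**What to change.** Amend the timing sentence in the Prehospital setting section and the matching analysis text:

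1. Record the CCHR items and the overall positive or negative call before handover wherever possible, and do not revise them using ED information. Other fields may follow afterwards.
2. Record completion time relative to handover, using the REDCap entry time and a time field on the paper CRF. An entry time shows when data were entered, not when the judgement was made, so it is only a marker.
3. Keep all forms in the main kappa and accuracy analyses. Add a sensitivity analysis restricted to forms completed before handover.
4. Report the share of forms completed before handover as a feasibility result.

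The restricted set should not become the main analysis. It could halve the sample, and forms may be late for reasons tied to the patient or the workload, which would introduce selection.

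Recruitment was already under way in April 2024, so for forms already collected, any available entry times can serve the sensitivity analysis. The cost is one added field, a small training change, and a restricted analysis that is less precise and open to selection. No sample size or progression criterion changes, and patient care is unaffected.

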#### In-hospital environment

REDCap will be used to collect hospital data, and a paper CRF will also be available as an alternative. Emergency physicians at the receiving hospital will assess the patients to determine whether a CT scan is necessary in accordance with local and national guidelines. Relevant data about imaging studies undertaken and their findings will be extracted from hospital records. The routine radiology reports will be used to extract the follow-up data required for this study. Where there is uncertainty about the interpretation of the radiology report, a second radiologist will be asked to interpret the images.

Further, emergency physicians at the receiving hospitals will be asked to assess the patients using the CCHR and record their findings, blinded to the assessments made by participating paramedics. These data will be used to determine the interobserver reliability of the CCHR between paramedics in the prehospital environment and clinicians in the ED. Additionally, in-hospital medical records will be reviewed to obtain information regarding neurosurgical interventions undertaken during the patient’s hospital admission.

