The National Institute for Health and Care Excellence (NICE) has guidelines that largely follow the CCHR to determine when to perform CT scans in cases of head injury.^12^ This approach is supported by evidence showing that the CCHR rule is the most cost-effective among various decision rules evaluated.^13^ Although the number of CT scans has increased, the admission rate has been halved (from 9% to 4%), resulting in a saving of £3381 per 100 patients.^14 15^ The implementation of NICE head injury guidelines indicates that the higher costs of CT scans, averaging about £100 per scan, are balanced by the savings from reduced hospital admissions, estimated to be around £847 per patient.^13^

Considering that paramedics have access to all the necessary data for the CCHR, it might be feasible to use the CCHR in the prehospital setting to promote consistency in care and optimise resource utilisation. Prehospital implementation of the CCHR could enable paramedics to transport patients to lower-level or non-trauma centres, or even (if shown to be sufficiently sensitive) safely leave patients at the scene. However, no studies have explored whether clinical decision aids can be used to rule out neurosurgically significant TBI in patients with apparently mild TBI in the prehospital field.

In England and Wales, around 1 million emergency department (ED) visits annually are for head injuries, with 90% being minor (Glasgow Coma Scale (GCS) 13–15), and the majority of patients are transported by ambulance services.^16^ Optimising healthcare resource use and enhancing patient care experiences can be greatly advanced by reducing unnecessary ambulance transports to distant MTCs, when appropriate and feasible.^17 18^ Integrating the CCHR into prehospital field presents a valuable opportunity to improve the triage process, allowing prehospital care providers to make informed decisions regarding the necessity of hospital transport and the level of care required, thereby optimising healthcare resources and potentially reducing healthcare costs. This approach also opens the door to exploring alternative care pathways for such patients, ensuring they receive appropriate and timely care without overwhelming hospital resources.

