#### Follow-up

Following the initial presentation to the ED, patients will be followed up to the time of hospital discharge. Data will be collected from the clinical records of the patient, including, but not limited to:

GCS on arrival in hospital.Details of the clinician’s assessment of the CCHR.Outcome of any brain imaging (ie, CT and/or MR scans, recorded as part of routine practice).AIS in relation to head injury.Injury Severity Score.Mortality status.Neurosurgical procedures and/or surgery.

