### Data analysis

#### Quantitative data

A descriptive analysis will be conducted based on the baseline data for patients enrolled in the study to characterise the demographic and clinical profile. This will include the number of eligible participants who were approached, the proportion who consented to participate, data completeness (expressed as number and percentage) for each variable collected and number and percentage of participants completing follow-up. We will also report recruitment data as rates (number of participants enrolled per week across the study period).

The interobserver reliability between paramedics and emergency physicians’ use of the CCHR will be calculated using Cohen’s kappa, a statistical method for measuring agreement between two observers, together with 95% CIs. Additionally, we will report upon the CCHR’s diagnostic performance for ruling out clinically significant TBI. This will be achieved by calculating the sensitivity, specificity, positive and negative likelihood ratios with 95% CIs against a reference standard of traumatic intracranial lesion, which will be identified from in-hospital records. Given the nature of this feasibility study, the analyses will be viewed as exploratory, preliminary and will be descriptive in nature. Furthermore, to determine the acceptability of the CCHR, the OADRI average item scores will be calculated, with higher scores indicating greater acceptability.

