### Safety considerations, adverse events and serious adverse events

Given the nature of this study, any risk to participants is very low. It is important to note that this study is observational in nature: a patient’s participation in this study will have no effect on the quality of medical care they usually receive in both prehospital and hospital settings. Our study will have no impact on the decision to undergo a CT scan as this will be undertaken at the discretion of the treating clinician, as part of routine clinical care, in accordance with current national guidance. The study will also have no effect on the decision to transport patients to the hospital. There are also small risks associated with data management, but we have carefully considered how data will be handled during the study and we will operate in accordance with current legislation and the standard operating procedures of the sponsor organisation to mitigate that risk. We are not aware of any potential risks this study would pose to the researchers.

Because of the low-risk nature of the study, we do not anticipate any adverse events (including serious adverse events) as a result of participating in this research. However, given the patient group (patients with suspected TBI), we anticipate that many patients will experience expected adverse events, which are related to their initial injury. We will not ask sites to report expected adverse events. Expected serious adverse events include, for example, death due to head injury, neurosurgical procedures for TBI, admission to hospital for traumatic brain injury and loss of function due to TBI. Unexpected adverse events and serious adverse events should be reported. Adverse events will be defined in accordance with ICH (International Council for Harmonisation)Good Clinical Practice as any untoward medical occurrence in a participant, but will only be reported if this was not expected as a result of the patient’s condition, up to the point of handover in hospital.

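### CT is ordered under guidance close to the rule being tested, so lesion sensitivity will probably look too high and LR− too low, and the article neither bounds nor names this

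*Protocol article*

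**What the plan says.** - **Who is scanned.** Under In-hospital environment, emergency physicians will "assess the patients to determine whether a CT scan is necessary in accordance with local and national guidelines". The safety section repeats that the study leaves the CT decision alone: "this will be undertaken at the discretion of the treating clinician, as part of routine clinical care, in accordance with current national guidance". There is no study-mandated CT.
- **How that guidance relates to the index test.** The Introduction states that NICE "has guidelines that largely follow the CCHR to determine when to perform CT scans in cases of head injury".
- **Reference standard.** Under Quantitative data, diagnostic performance is assessed by "calculating the sensitivity, specificity, positive and negative likelihood ratios with 95% CIs", and this is done "against a reference standard of traumatic intracranial lesion, which will be identified from in-hospital records". The imaging available is what routine care produced (Follow-up).
- **Follow-up.** After the ED presentation, "patients will be followed up to the time of hospital discharge".
- **Status of the analysis.** Accuracy is the last of the four objectives: "To obtain an estimate of the diagnostic accuracy of the CCHR when used in the prehospital setting". Quantitative data describes the analyses as exploratory and descriptive. No accuracy measure appears in the progression criteria (Table 2).
- **What the article does not say.** It does not state how a patient without a scan is classified for the lesion endpoint. Neither the Outcomes section nor Table 2 includes CT use by rule result.

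**The concern.** The criteria of the index test largely influence who receives the test that defines the reference standard. This is partial verification dependent on the index test. A lesion in a rule-negative patient is less likely to be imaged, hence less likely to be recorded, and false negatives drop out of the sensitivity calculation faster than true positives do.

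Sensitivity and LR− are the quantities that matter for ruling out injury. The Introduction links possible non-conveyance to the rule proving sensitive enough, and the Impact section says that the findings will inform the full accuracy study. An error towards higher sensitivity is therefore in the unsafe direction. It is systematic: the 95% CIs do not show it, and a larger study with the same design would repeat it with narrower intervals. A feasibility study is the natural place to learn how often rule-negative patients are scanned.

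**Working it through.** **The plan's own figures.** The article gives no expected sensitivity, lesion prevalence or CT rate, so there is no accuracy figure to reproduce. Its one derived number, about 1100 eligible patients, follows from 5332 / 57 months × 6 months × 2 centres = 1122.5, but the point does not rest on it.

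**Inputs.** From the article: the CT rule, the reference standard, the end of follow-up, about 100 participants, and a CCHR specificity range of 36–65% (Introduction). Assumed: true sensitivity Se, lesion prevalence, and the CT rates v+ and v− in rule-positive and rule-negative patients.

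**Sensitivity.** If a lesion is recorded only when imaged, and v+ and v− are the CT rates among patients with lesions:

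apparent Se = Se·v+ / [Se·v+ + (1 − Se)·v−]

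This exceeds Se exactly when v+ > v−. Prevalence cancels.

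| v+ | v− | True Se 90% appears as | True Se 80% appears as |
|---|---|---|---|
| 90% | 10% | 98.8% | 97.3% |
| 90% | 30% | 96.4% | 92.3% |
| 90% | 50% | 94.2% | 87.8% |
| 70% | 50% | 92.6% | 84.8% |
| 70% | 70% | 90.0% | 80.0% |
| 70% | 90% | 87.5% | 75.7% |

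For example, 0.90 × 0.90 / (0.90 × 0.90 + 0.10 × 0.30) = 0.81 / 0.84 = 96.4%, and 0.63 / (0.63 + 0.05) = 92.6%. With equal rates the bias vanishes; with the order reversed it changes sign.

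**Specificity and LR−.** These depend on how unscanned patients are handled. Take N = 100, prevalence 10%, Se 90%, Sp 50%, v+ = 90%, v− = 30% (all assumed except N), with the same CT rates in patients without lesions. The true LR− is 0.10 / 0.50 = 0.20.

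- Recorded true positives: 10 × 0.9 × 0.9 = 8.1. Recorded false negatives: 10 × 0.1 × 0.3 = 0.3. Apparent Se = 8.1 / 8.4 = 96.4%.
- *Unscanned counted as lesion-free:* true negatives 45 + 0.7 = 45.7 and false positives 45 + 0.9 = 45.9. Specificity = 45.7 / 91.6 = 49.9%, and LR− = 0.0357 / 0.499 = 0.07.
- *Unscanned excluded:* true negatives 45 × 0.3 = 13.5 and false positives 45 × 0.9 = 40.5. Specificity = 13.5 / 54 = 25%, and LR− = 0.0357 / 0.25 = 0.14.

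Both readings make LR− too favourable, and they give very different specificities from the same patients.

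**How many could be unverified.** With N = 100, prevalence 10%, Se 80% and the article's specificity range, rule-negatives number 90 × 0.36 + 2 = 34.4 to 90 × 0.65 + 2 = 60.5. If 10–30% of them are scanned, between 34.4 × 0.7 = 24 and 60.5 × 0.9 = 54 have no scan.

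**The case against.** The strongest case against the point has five parts.

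1. **The index test and the CT trigger are not the same assessment.** The index test is the paramedic's modified rule. The ED physician reassesses blinded to it, under guidance that only largely matches the CCHR, and with discretion. A paramedic-negative patient whom the ED finds positive is scanned in the ordinary course. A reader might infer that rule-negative patients simply go unscanned, or that a false negative surfaces only if a clinician departs from the guideline. The documents support neither; they support only a probable difference in CT rates.
2. **No classification rule is given.** A reader might infer that unscanned patients are entered as true negatives. Quantitative data says only where lesions are looked for. The rule could sit in a fuller document, and its absence alone would not be a finding. The point survives because counting unscanned patients as lesion-free and excluding them both give a biased LR−.
3. **Other outcomes are checked.** Clinicians blinded to the CCHR result review records for neurosurgically significant TBI and death within 7 days. These are less exposed, but that does not repair the lesion analysis: blinding cannot recover scans that were never done.
4. **The size is assumed.** Patients with lesions may be symptomatic and scanned anyway, so v− could be high. The modified rule counts anticoagulant and antiplatelet users and any GCS below 15 at presentation as positive, so v+ may fall short of 90%. With 70% and 50% the shift is only 2.6 points. Random error may be larger: 10 of 10 lesions detected gives an exact 95% CI of 69–100%. This stands as a limit on the size, not on the direction.
5. **The analysis is exploratory, the limited sample is declared, and care is unchanged.** This lowers the severity. Those caveats concern precision, however, and this is bias.

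**Conclusion.** The point holds as a probable upward bias in lesion sensitivity and a downward bias in LR−. It rests on three conditions:

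- Lesions become known only through routine imaging.
- Among patients with lesions, CT is more frequent in paramedic-rule-positives than in rule-negatives. The article's account of the guidance makes this likely but does not establish it.
- Nothing after discharge reveals lesions missed earlier.

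The article does not give the size. For a true sensitivity of 90%, the assumed rates with v+ > v− shown above give apparent values from 92.6% to 98.8%. A reader might go further and treat this as a defect that must be cured before the study can be used. The documents do not support that: accuracy is exploratory and no progression decision depends on it. It should be fixed, because accuracy is a stated objective and is meant to inform the definitive study.

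**What to change.** In Data analysis, Quantitative data:

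- Treat patients without a scan as unverified for the lesion endpoint, neither lesion-free nor silently dropped.
- Report the numbers scanned and unscanned by paramedic CCHR result, and add this table to the feasibility outcomes.
- Give sensitivity, specificity and likelihood ratios in verified patients, with best- and worst-case bounds for the unverified.
- Name partial verification as a limitation that the 95% CIs do not cover.
- Report accuracy alongside for neurosurgically significant TBI, which the Abstract already calls the primary clinical outcome, from the records already planned. Note that the head AIS ≥3 component, in the definition under Measuring and defining outcomes, may itself depend on imaging.

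A Begg-Greenes correction is optional. It needs enough scanned rule-negatives, which may not be available, and it assumes that scanning depends only on recorded variables.

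**Cost.** Analysis wording and a cross-tabulation; imaging data are already collected, and no change to who is scanned is implied. The downside is wider and less favourable intervals. In the worked example, 46 × 0.7 = 32.2 rule-negatives are unscanned, and if all had lesions sensitivity would fall to 8.1 / (8.1 + 0.3 + 32.2) = 20%. That width shows how little the lesion endpoint can say about ruling out injury. Follow-up beyond discharge would help but is not part of this low-cost change: the study is already recruiting, and extending follow-up could need an approved amendment.
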